## Abstract

**Background:**

Tobacco use is the leading cause of preventable death in Ireland with almost 6000 smokers dying each year from smoking-related diseases. The ‘We Can Quit2’ (WCQ2) study is a pilot pragmatic two-arm, parallel-group, cluster randomised trial that aims to explore the feasibility and acceptability of trial processes including recruitment and to estimate parameters to inform sample size estimates needed for an effectiveness trial. This future trial will assess the effectiveness of a community-based smoking cessation intervention for women living in disadvantaged areas on short- and medium-term cessation rates.

**Methods/design:**

Four matched pairs of districts (eight clusters) selected by area level of deprivation, geographical proximity, and eligibility for free medical services will be randomised to receive either WCQ (behavioural support + access to Nicotine Replacement Therapy (NRT)) delivered over 12 weeks by trained Community Facilitators (CFs) or to a form of usual care, a one-to-one smoking cessation service delivered by Smoking Cessation Officers from Ireland’s national health service, the Health Service Executive (HSE). Within each cluster, 24–25 women will be recruited (97 per arm; 194 in total) in 4 phases with consent obtained prior to cluster randomisation. The outcome measures will assess feasibility and acceptability of trial processes, including randomisation. Outcome data for a future definitive intervention (biochemically validated smoking abstinence) will be collected at end of programme (12 weeks) and at 6 months. WCQ2 has an embedded process evaluation using both qualitative and quantitative methods. This will be conducted (semi-structured client and CF interviews, intervention delivery checklist, and diary) to explore acceptability of trial processes, intervention fidelity, trial context, and implementation. Trial processes will be assessed against domains of the PRECIS-2 wheel to inform a future definitive trial design.

**Discussion:**

Data from this pilot trial will inform the design and sample size for a full cluster randomised trial to determine the effectiveness of an intervention tailored to disadvantaged women in improving smoking cessation rates. It will provide transferable learning on the systems and implementation strategies needed to support effective design of future pragmatic community-based trials which address health promotion interventions for women in disadvantaged communities.

**Trial registration:**

Concurrent to publication. Controlled trials ISRCTN74721694.

## Background

Tobacco use is the leading cause of preventable death globally. Almost 6000 smokers die annually in Ireland from smoking-related diseases [1]. The Tobacco Free Ireland Programme have set a target for Ireland to become tobacco free (i.e. with a smoking prevalence rate of less than 5%) by 2025 [2]. Although smoking rates have dropped by 1% per year since 2015, 20% of the population aged 15 years and over remained regular smokers in 2018 (men 22%; women 17%) [3]. The data confirm persistence of the health inequalities gap with higher rates in more disadvantaged than in more affluent areas (26% vs 16%) [3]. It is evident therefore that ‘business as usual’ is not sufficient to affect the step change required to reach the endgame [4].

Whereas lung cancer incidence rates in Irish males declined steadily during 1994 to 2015, female rates increased significantly and continue to increase [5]. More women in Ireland are now dying from lung cancer (19% of all cancer deaths) than breast cancer (17%) [6]. In socio-economically disadvantaged areas, lung cancer rates are higher in women than in men [5]. This pattern suggests that smoking impacts on health inequalities via gender in addition to socio-economic influences.

Research has also noted the cumulative effect of disadvantage on women’s smoking [7]. The intergenerational impacts of women smoking are particularly evident in disadvantaged communities, with increased likelihood of potentially preventable adverse outcomes perinatally, during infancy and childhood [8]. Measures to restrict impact of environmental tobacco smoke in the home are less likely to be implemented [9], and parental smoking in the home increases the child’s chances of becoming an adult smoker (via role modelling) which has direct and immediate impact on children’s health [10].

Previous studies have made the case that smokers from disadvantaged groups should be targeted for greater efforts to support smoking cessation, with more consideration of the role of gender in design of smoking prevention interventions. Such efforts need to focus on the social conditions that affect women’s lives as well as the individual level interventions including approaches to improve health behaviours [7].

The link between cancer and smoking among women in Ireland, and other developed countries, has been recognised by the World Health Organisation (WHO) through the Framework Convention on Tobacco Control [8]. The WHO has called for a gendered lens to be applied to tobacco control policies. Despite this, few countries have attempted to tailor smoking cessation services to meet the needs of women.

The national Health Service Executive (HSE) provides smoking cessation services which are not gender-based. This service is available to any Irish citizen. The universal components of this service are a National Quit service, which was launched in 2014 as an interactive smoking cessation support service delivered via phone, web, text, and social media. These elements may be supported by specialist smoking cessation services locally that provide face-to-face behavioural support either individually or group based (rarely) and access to Nicotine Replacement Therapy (NRT); however, this is resource dependent [9]. A map of the Irish smoking cessation services is available at the following link: https://quit.ie/I-Want-to-Quit/Support-Services/.

### WCQ

Arising from the above context and in a bid to design and deliver an intensive, face-to-face smoking cessation intervention tailored to women that is feasible in an Irish context, the Irish Cancer Society (ICS) in partnership with the National Women’s Council Ireland, and the Institute of Public Health in Ireland developed ‘We Can Quit’ (WCQ), a community-based smoking cessation programme for women from socially and economically disadvantaged communities.

The WCQ intervention was developed in accordance with the Medical Research Council guidance for developing complex interventions, identifying the evidence base, identifying/developing theory, and modelling process and outcomes [10]. It was developed based on evidence that delivery of a group programme to disadvantaged US women in their local communities by trained peers (sister-to-sister) [11, 12] using behavioural support and access to pharmacotherapy [13] resulted in higher than expected smoking cessation rates in this group of women. The intervention was adapted by the ICS and HSE for an Irish setting, using a community social-ecological model [14] and optimised in a prior feasibility study of 39 women which showed favourable retention and smoking cessation rates [15].

The core components of the WCQ intervention are as follows:
An evidence-based smoking cessation behavioural support programme delivered in a group setting over 12 weeks with individual follow-up as required for women from disadvantaged communitiesCombination NRT (nicotine patches and an oral NRT product dispensed by community pharmacists free of charge)Delivery by trained community health workers to women in their community settingInclusion of a relapse prevention element

Additional non-core components include the following:
Signposting/additional community supports by local community health workers to participants who enrol in the programmeUse of social marketing strategies to promote cultural change and promote cessation services

The principal differences with the standard HSE programme are the tailoring of WCQ to women in a group community setting, delivery by community lay personnel over 12 weeks as opposed to an average of 6–7 individual sessions, and NRT provided free of charge to all participants instead of a means-tested service within the HSE.

The 12-week programme was modified for this pilot cluster randomised controlled trial (RCT)—WCQ2, by revision of the intervention manual and standardisation of all questionnaires to include validated questions. This protocol describes the WCQ2 RCT which incorporates an embedded process evaluation.

### Aims

The overall aim of the study is to assess the feasibility of running a definitive randomised trial to determine whether a community-based smoking cessation complex intervention tailored to disadvantaged women affects their smoking cessation rates.

### Objectives

The primary objectives of the trial are as follows:
(i)To determine the feasibility and acceptability of trial processes including randomisation of districts, recruitment, and data collection in both intervention and control arms(ii)To assess data quality and completion rates for the main outcome measures for a future definitive trial (DT) including biochemically validated abstinence from smoking (using salivary testing) at 12 weeks (end of programme) and 6 months (longer-term outcome)(iii)To estimate the sample size and design for a future DT including an estimate of the intra-cluster correlation coefficient (ICC) to account for the effect of ‘clustering’ in design and analysis

The secondary objectives of the trial are as follows:
(i)To test the robustness of trial design with respect to context for delivery of the intervention, implementation processes, and key mechanisms of impact, from which to optimise design of a full effectiveness trial(ii)To develop strategies to optimise recruitment and dissemination of findings to trial stakeholders to inform knowledge exchange and future research

The study protocol (version 3.0, 19 October 2018) has been developed in line with the Standard Protocol Items: Recommendations for Interventional Trials (SPIRIT) 2013 statement [16] (Additional file 1). Any changes to the protocol will be communicated to all investigators, submitted for ethical approval, and reflected in changes to the trial registry.

## Methods/design

This study is a pilot two-arm, parallel group, cluster randomised trial [17]. It was designed with assistance from the Irish Health Research Board Trials Methodology Research Unit (HRB-TMRN).

### Setting, recruitment, and informed consent

#### Cluster recruitment

Four matched pairs of urban and semi-rural districts (eight clusters) in Dublin and Cork will be identified in advance where local communities have expressed interest in participating via Local (Area) Advisory Groups (LAGs).

LAGs have been developed, with two in Dublin and two in Cork, through a community engagement process initiated and developed by the ICS in partnership with a company in the local community and are government funded. They consist of the ICS, the Local Development Company, community development projects, family resource centres, representatives from the HSE, local authorities, local pharmacies, and other relevant community groups, such as traveller, women, and youth organisations.

Their function is to establish support for community action on cancer prevention, including provision of community-based smoking cessation services for disadvantaged groups. In the WCQ2 study, their role will be to direct and deliver a local recruitment strategy. They will support the delivery of the research project in their designated areas.

Criteria for selection of the four matched pairs of districts by the LAGs will be similarity in terms of population size where we aim to include approximately 8,000 - 10,000 women per district, deprivation using the 2016 Pobal HP Deprivation Index [18], and feasibility such as availability of a one-to-one national smoking cessation service in the chosen areas. The selected LAGs will be asked to provide informed consent based on their understanding of randomisation of their district to either an intervention or a control arm.

### Participant recruitment

#### Eligibility criteria

Women will be invited to take part in the study if they are 18 or over, speak fluent English, self-report as daily smokers, indicate an interest in quitting, are deemed to live/work/reside within easy travel distance of trial catchment areas, are taking NRT, or have been prescribed bupropion/varenicline by the doctor at time of recruitment and women using e-cigarettes who are current smokers.

#### Exclusion criteria

The following participants will be excluded from the study: women who are pregnant or planning a pregnancy in the near future, women already enrolled in another smoking cessation study, those who cannot travel to location of programme delivery, women who use NRT/bupropion/varenicline/e-cigarettes who have not smoked cigarettes in the 7 days prior to recruitment, and women who do not have the capacity to give informed consent.

### Sample size

In the previous WCQ feasibility study, two areas in Dublin were targeted with populations of 7800 and 8000, respectively. In total, 39 women signed up for the programme, evenly split between the two areas (20 in one area and 19 in the other), and of these, 29 women (74%) were retained at 12 weeks follow-up [15]. Subsequent WCQ programmes (February 2015 to April 2016) have demonstrated this retention rate was maintained at 62% (83/133) (Irish Cancer Society, personal communication). Therefore, based on this existing evidence, if 194 women (97 per arm) are recruited into the study, 120 women are predicted to be in this pilot study by 12 weeks [19]. This will be sufficient to identify potential problems in practicality/feasibility, which have a 5% probability of occurrence [20]. In the previous feasibility study [15], 50% of women who made contact were subsequently recruited to one of two 12-week programmes running concurrently in one district (morning or evening programmes), corresponding to approximately 20 women per programme. If the WCQ programme is run sequentially in 4 districts with 2 concurrent WCQ groups each time (i.e. 8 programmes), then there is potential to recruit up to 160 women during the period January 2018 to June 2019 (18 months), thus exceeding the 97 required. However, the unknown parameters, which need to be estimated from this pilot trial, are the retention rates for the usual care districts, predicted to have much lower rates. Data will also be used to estimate the intra-cluster correlation (ICC), and this data together with recruitment and attrition rates will be used to inform the sample size for the DT. A flow diagram of the study design is attached (Fig. 1). It will be conducted in keeping with the CONSORT statement extended for reporting cluster RCTs [21].

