### Randomisation and allocation concealment

Four matched pairs of districts (eight clusters) will be randomised with each matched pair of clusters randomised to intervention or controls in a 1:1 allocation ratio. The randomisation will follow a pragmatic approach whereby paired districts ready for the intervention will be randomised first, followed by the next available matched pair; this accounts for temporal changes and will provide a balanced design.

The randomisation will be conducted remotely by the Wellcome Trust Clinical Research Facility (CRF) independent of the Trial Management Team, who will develop a standard operating procedure for this process. The code for each matched pair of districts will be concealed and securely stored by the Wellcome CRF at St. James’s Hospital. It will be revealed to the WCQ2 trial team once sufficient numbers have been recruited (or by agreement with the Trial Management Group (TMG) if recruitment is insufficient prior to intervention delivery). Practitioners will be informed of the area in which they will deliver their programme by the research team, and participants will be informed of their allocation by the practitioners. Figure 1 displays an overview of cluster randomisation process.

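### The 120 women predicted at 12 weeks apply the retention of WCQ programmes to both arms, although the plan expects much lower retention in usual care

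*Protocol article*

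**What the plan says.** The Sample size section of the protocol article cites two 12-week retention rates. In the earlier feasibility study of 39 women, "29 women (74%) were retained at 12 weeks follow-up". Later programmes gave 62% (83 of 133). Both rates come from women who attended WCQ; neither describes the HSE one-to-one service.

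From this evidence the section concludes that "if 194 women (97 per arm) are recruited into the study, 120 women are predicted to be in this pilot study by 12 weeks". The next sentence draws the consequence: "This will be sufficient to identify potential problems in practicality/feasibility, which have a 5% probability of occurrence". It gives no confidence level and does not say whether each arm or the whole pilot is meant.

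Later in the same paragraph the plan names what is still unknown: "the retention rates for the usual care districts, predicted to have much lower rates". Allocation is 1:1 within matched pairs, so half of the 194 women are in usual care.

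**The concern.** A single retention rate, taken from the intervention, is applied to all 194 women, and a few sentences later the plan says that half of them are expected to do much worse. The total of 120 therefore does not reflect the plan's own expectation.

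The figure is the only stated forecast of how many women will provide 12-week data, and the statement about identifying problems rests on it. Primary objective (i) covers "recruitment, and data collection in both intervention and control arms", and retention is a secondary outcome by arm. If the 120 stands, control-arm losses that the plan itself expected could later be judged against a total that never allowed for them. A reader may also assume about 60 control women at 12 weeks and take the 5% statement to hold in that arm by itself.

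**Working it through.** **Inputs.** From the Sample size section: 194 women, 97 per arm; WCQ retention 29/39 = 74% and 83/133 = 62%; a predicted 120 at 12 weeks; a problem probability of 5%. Assumed, because the plan gives no figure: usual-care retention (20–60% shown) and a confidence level of 95% (90% also shown).

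**1. Reproducing the 120.** Women retained = women recruited × retention.
- 62% in both arms: 194 × 0.62 = 120.3, or 97 × 0.62 = 60.1 per arm. This reproduces the 120.
- 74% in both arms: 194 × 29/39 = 144.3. It does not.
- The two sources pooled: 194 × 112/172 = 126.3. It does not.

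So 120 is obtained from the later WCQ rate applied to the control women as well.

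**2. Women needed for a 5% problem.** The chance of seeing at least one case among n independent women is 1 − 0.95^n. Setting this to the confidence level c gives n = ln(1 − c)/ln(0.95).
- c = 95%: 58.4, so 59 women.
- c = 90%: 44.9, so 45 women.

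**3. Prediction by arm.** WCQ is kept at 62% (60 women) and usual-care retention is varied. The last column is the smallest problem probability that the control arm alone would show at least once with 95% chance, 1 − 0.05^(1/n).

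| Usual-care retention (assumed) | Control women | Total | Chance of seeing a 5% problem, total | Same, control arm alone | Smallest problem, control arm |
|---|---|---|---|---|---|
| 62% (as implied) | 60 | 120 | 99.8% | 95.4% | 4.9% |
| 60% | 58 | 118 | 99.8% | 94.9% | 5.0% |
| 50% | 49 | 109 | 99.6% | 91.9% | 5.9% |
| 40% | 39 | 99 | 99.4% | 86.5% | 7.4% |
| 30% | 29 | 89 | 99.0% | 77.4% | 9.8% |
| 20% | 19 | 79 | 98.3% | 62.3% | 14.6% |

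**4. Thresholds in the control arm.** At 95% confidence the arm has enough women only if retention is at least 59/97 = 60.8%. At 90% the limit is 45/97 = 46.4%. For the whole pilot there is no such limit as long as WCQ retention is 62%, because its 60 women alone give 1 − 0.95^60 = 95.4%.

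**5. Which problems are affected.** A problem at recruitment or consent can be seen in all 97 control women: 1 − 0.95^97 = 99.3%. Only problems visible solely in women still present at 12 weeks depend on control retention.

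**The case against.** The strongest reply is that the paragraph discloses its own uncertainty: it says openly that usual-care retention is unknown and must be estimated. The pilot is mainly descriptive, with no formal significance testing, and neither the recruitment target nor the primary outcome depends on the 120. This stands, and it limits the severity.

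It can also be said that a total of 120 is not impossible with unequal arms. At the other cited WCQ rate, 72 women would remain in that arm, and 120 would then need 48 of 97 in usual care (49.5%). That is true, so the fault is an unsupported assumption about the control arm, not an arithmetical impossibility. But the plan states no such split, and 62% in both arms gives its figure directly.

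Three stronger readings are tempting and are not supported.
- A reader might infer that the 5% statement is wrong as written. It is attached to the 120 women of the whole pilot, and read that way it survives at every usual-care rate in the table. A per-arm intention is plausible, since 60/0.62 = 96.8 rounds up to 97, but 120/0.62 = 193.5 equally rounds up to 194, and the text does not say which was meant. The 95% level is likewise an assumption.
- A reader might infer that 62% would be carried into the definitive trial for both arms. The plan says the opposite: the pilot's own recruitment and attrition rates will inform that sample size, and the Secondary outcomes section measures retention in each arm.
- A reader might test the statement against problems arising at district level. The plan makes no claim about detecting those.

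**Conclusion.** The point holds for the 120. It applies WCQ-only retention to usual care, against the expectation stated in the same paragraph, and is therefore too high. With usual-care retention assumed at 30–50%, the total is 89–109, which is 11–31 women fewer than stated. The size rests on that assumed range and on WCQ retention staying at 62%; the direction rests only on the plan's own words.

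The 5% statement holds for the pooled sample at 95% confidence. In the control arm alone, for problems visible only at 12 weeks, it does not hold at 95% once retention is below about 61%. At 30–50% retention the chance is 77–92%, treating women as independent. This is a limit on how far the statement reaches, not an error in it as written. Severity is minor to moderate.

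**What to change.** In the Sample size section:
- Replace the 120 with a prediction by arm: about 60 of 97 in WCQ, and for usual care a range chosen by the trial team and labelled as an assumption. The 30–50% used here (29–49 control women, 89–109 in total) is an illustration, not a sourced figure.
- State the confidence level of the 5% statement and that it refers to the pooled sample. At 95% this requires 59 women.
- Add that, for problems seen only in women still present at 12 weeks, it does not hold at 95% in the control arm alone if retention there is below about 61%, and that the calculation treats women as independent.

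The cost is a few sentences. No extra participants and no change of design or outcome are needed, but a stated figure becomes less favourable.

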### Outcomes

#### Primary outcome

The primary study outcome is assessment of whether the recruitment target of 8 districts (clusters) and 194 women is achievable within 18 months of programme start. The recruitment rate will be estimated for each wave. It will be defined as the number of women who consent to participate (the numerator), divided by the number of eligible women who have registered with the programme.

The four matched pairs of disadvantaged geographical districts (clusters) will be based on the number of eligible women within in each matched pair of districts (approx. 16,000–20,000). Each pair will be randomised to intervention or to usual care. Subsequent recruitment of 24–25 women who consent to participate in each of the eight districts (97 in each trial arm) will occur during four 12-week periods. The percentage of eligible women needed to plan a DT will be estimated.

Eligibility rates will be established from registration details entered by either the participant or a person acting on their behalf (e.g. GP) on the WCQ2 webpage. Contact details of potential participants will be recorded at the point of expression of interest. Dropout rates will be calculated between time of confirmation of eligibility and time of consent. Number of consented women will be recorded prior to randomisation.

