### Data analysis

The pilot data will be analysed on an intention-to-treat basis and will be mainly descriptive. A per protocol analysis will also be carried out. A separate statistical analysis plan will be produced. In brief, descriptive analyses will summarise baseline characteristics of women in each trial arm, eligibility rates, recruitment rates, participation, and attrition rates in preparation for a full trial. Subgroup analysis by GMS eligibility will be carried out. Elements of the RE-AIM (Reach, Effectiveness, Adoption, Implementation, and Maintenance) evaluation tool will provide a suitable framework to structure this analysis [34]. As this study is not powered to detect significant differences between groups, formal significance testing will not be carried out. The future trial primary outcome will be the comparison of the proportions of women between groups who self-report having quit smoking, corroborated by laboratory testing such as salivary cotinine at end of programme (12 weeks). The number of participants (%) experiencing cessation will be summarised between groups. The mean change scores (with 95% CIs) between groups on a range of questionnaires will be estimated, to assess whether these were in the expected direction of effect. An assessment of normality will be made on questionnaire scores, and parametric (means and SDs) and/or non-parametric estimates and variability (median/IQR) will be reported at baseline, 12 weeks, and 6 months. Descriptive analysis of secondary outcomes will summarise means and standard deviations for continuous outcome measures or numbers (%) for categorical data at baseline, 12 weeks, and 6 months.

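### An ICC from eight districts is one input to the definitive-trial sample size, but the pilot's size justification does not address its precision, and the between-arm intervals should be tied to the district

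*Protocol article*

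**What the plan says.** Objectives, primary (iii), covers the sample size and design of the definitive trial, "including an estimate of the intra-cluster correlation coefficient (ICC) to account for the effect of" clustering. The Sample size section repeats this: "Data will also be used to estimate the intra-cluster correlation (ICC), and this data together with recruitment and attrition rates will be used" for the definitive trial's sample size.

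On the number of clusters, Randomisation and allocation concealment states "Four matched pairs of districts (eight clusters) will be randomised", with each pair "randomised to intervention or controls in a 1:1 allocation ratio".

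The size of the pilot is justified in women: "if 194 women (97 per arm) are recruited into the study, 120 women are predicted to be in this pilot study by 12 weeks". That number is then called enough to reveal feasibility problems that have a 5% probability of occurring. The section gives no expected precision for the ICC, no external ICC, and no plan for using an uncertain estimate.

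Data analysis is a short summary that announces a separate statistical analysis plan. It says: "The mean change scores (with 95% CIs) between groups on a range of questionnaires will be estimated", and the results are then read for whether they point the anticipated way. District and pair are not mentioned there. The same section calls the analysis mainly descriptive and rules out formal significance tests.

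**The concern.** The precision of an ICC depends mainly on the number of clusters. Here that number is eight, and each arm or pair effect removed costs degrees of freedom. The ICC enters the definitive trial through the design effect, which multiplies the whole sample size, so good recruitment and attrition data cannot make up for a poor ICC. Taken at face value, a chance estimate at or below zero would size the next trial as if women were individually randomised. A chance high estimate could make a feasible trial look out of reach.

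The second part is smaller. Between-arm intervals for questionnaire scores, read for direction, come from four districts per arm. The summary fixes raw change as the measure although baseline scores are collected, and it does not tie the intervals to the unit that was randomised.

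**Working it through.** **1. The plan's own figure.** 194 × 0.62 = 120.3, so the stated 120 reproduces (194 × 83/133 = 121.1). The chance that 120 women show a 5% problem at least once is 1 − 0.95^120 = 0.998; 59 women would already give 95%. Both checks succeed. Both count women, and neither concerns variation between districts.

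**2. Information on the ICC.** Between-district degrees of freedom are 8 − 2 = 6 after arm, and 8 − 4 − 1 = 3 after pair and arm. Women per district are 194/8 = 24.25 at recruitment and 120/8 = 15 at 12 weeks.

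**3. Spread of the estimate.** The documents give neither an ICC nor an expected abstinence rate, so both are assumed. The simulation used beta-binomial data, eight equal districts, 20% abstinence, no arm effect and 40,000 runs. The estimator is ICC = (MSB − MSW) / (MSB + (m − 1) MSW) with arm removed.

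| True ICC | Women per district | Central 95% of estimates | Share ≤ 0 |
|---|---|---|---|
| 0.02 | 24 | -0.03 to 0.10 | 33% |
| 0.02 | 15 | -0.05 to 0.13 | 41% |
| 0.05 | 24 | -0.02 to 0.17 | 15% |
| 0.05 | 15 | -0.04 to 0.20 | 25% |

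With pairs also removed (3 df), the share at or below zero at ICC 0.02 is about 43% (24 per district) or 49% (15 per district). As the true ICC rises, a zero becomes less likely but the spread grows.

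**4. What this does to a sample size.** Design effect = 1 + (m − 1) × ICC. At 24 per district the true value for ICC 0.02 is 1 + 23 × 0.02 = 1.46. Estimates across the central 95% would imply anything from 1.0 (negative values set to zero) to 1 + 23 × 0.103 = 3.4.

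**5. The interval one pilot would report.** With F = (1 + (m − 1)r) / (1 − r), dividing F by its upper 2.5% point, or multiplying it by the reverse one, and converting back gives the 95% CI (normal theory, so approximate for abstinence). At 6 df, an estimate of 0.02 with m = 24.25 has a CI of -0.02 to 0.21. An estimate of 0.05 with m = 15 has -0.02 to 0.34, a design effect from 1.0 to 1 + 14 × 0.342 = 5.8. With 3 df the upper limit for that case reaches 0.62.

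**6. Between-arm intervals, if districts were ignored.** With 15 per district, the standard error would be too small by √(1 + 14 × ICC): √1.28 = 1.13 at ICC 0.02 and √1.70 = 1.30 at 0.05. Coverage of a nominal 95% interval (simulated on a proportion of 0.25, four districts per arm) is 91% and 86%; a continuous score gives 92% and 87%. A district-level t interval on 6 df holds about 95% and is about 1.35 to 1.56 times as wide on average.

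**7. Raw change against baseline adjustment.** For equal baseline and follow-up variances and correlation ρ, the variance of raw change is 2σ²(1 − ρ), and the baseline-adjusted variance is σ²(1 − ρ²). The ratio is 2/(1 + ρ). For an assumed ρ of 0.3, 0.5 or 0.7 it is 1.54, 1.33 or 1.18, in favour of adjustment. These are woman-level variances; the gain between districts depends on a correlation that the documents do not give.

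**The case against.** The best defence is that the protocol claims little. It says the ICC will inform the sample size alongside recruitment and attrition rates. It does not say that the point estimate will be plugged in alone, nor that external ICCs are excluded. Progression is judged with ADePT and PRECIS-2, with no ICC threshold. This stands against any claim that objective (iii) rests on the ICC alone. It does not answer the gap: the ICC is a named input to a primary objective, and the section that sizes the pilot is silent on how well it can be estimated.

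A reader might also infer from the silence on districts and pairs that the planned intervals will be too narrow. The documents do not support this. The text is a summary, a separate analysis plan is announced, the cluster extension of CONSORT is cited, and nothing says that women will be treated as independent. Silence on pairs would in any case point the other way, since ignoring effective matching tends to widen intervals. Nor is a four-pair t interval the only valid choice: much of its extra width is the 3-df multiplier (3.18/1.96 = 1.62), and a district-level interval on 6 df is also valid.

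Finally, the intervals concern questionnaire scores. Cessation is summarised as counts and percentages, and the study disclaims power and significance tests. That limits the harm of a directional reading but does not remove it.

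**Conclusion.** The ICC point holds. Eight districts cannot give an ICC precise enough to size a definitive trial alone, and the plan neither says so nor provides for it. The size of the problem depends on assumed values. At ICC 0.02 and 20% abstinence, about a third (24 per district) to about 40% (15 per district) of pilots would return zero or less; at ICC 0.05 the shares are 15% and 25%. Equal retention across districts is also assumed. The protocol expects much lower retention in usual care, which would reduce precision further.

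On the between-arm intervals, what holds is narrower. Baseline adjustment is a better choice than raw change and uses data already collected, one clause should tie the intervals to the district, and the direction of effect should be read as description only. Undercoverage (about 91% at ICC 0.02, 86% at 0.05) is conditional on districts being ignored, which the protocol does not say.

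**What to change.** - **Objectives (iii) and Sample size:** state that the ICC will be reported with its 95% CI, acknowledge that eight districts give low precision, and commit to sizing the definitive trial over a stated range that includes external ICCs, with the pilot estimate never the sole input.
- **Data analysis:** replace raw mean change with between-arm differences adjusted for the baseline score. State that the 95% CIs respect the randomised district, through a district-level analysis or a mixed model with small-sample degrees of freedom. The exact method can stay in the analysis plan.
- **Data analysis:** say that the direction of observed differences is descriptive only and is not evidence of effect.

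The cost is wording and a little analysis, with no change to trial conduct or data collection. The price is wider intervals than an analysis that ignored districts would give, and a more modest claim for objective (iii).
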